## Abstract

**Background:**

Mental healthcare is under pressure, resulting in prolonged waiting lists for treatment. This is problematic, as time spent on a waiting list is associated with suboptimal recovery, more treatment dropout, and increased societal costs. An online transdiagnostic positive psychology intervention (eHealth PPI) may increase resilience (i.e., the ability to adapt to challenging experiences) and well-being among patients. Offering the same intervention to loved ones could be a novel contribution to enhancing positive effects among patients and loved ones. A study protocol is presented aimed at examining the clinical effectiveness, cost-effectiveness and implementation procedures of an eHealth PPI for patients with various mental health complaints awaiting treatment and their loved ones.

**Methods:**

Using two studies, the current manuscript proposes a threefold evaluation of an eHealth PPI consisting of 9 modules, focusing on: [1] clinical effectiveness, [2] economic evaluation, and [3] implementation procedures. To evaluate the procedural implementation of the eHealth PPI from a user-perspective, a replicated single-case design (RSCD) will be performed in study 1, with measurements at baseline, after each module, and post-intervention. In study 2, a randomized controlled trial (RCT) will be used to examine the clinical effectiveness, cost-effectiveness and implementation procedures of the eHealth PPI, using three arms: [1] PPI during the waiting period for patients, [2] PPI during the waiting period for patients and loved ones, and [3] treatment as usual (TAU), i.e., the conventional waiting period for patients. Following the waiting period, patients will receive a mental health treatment as usual. Study 2 will employ measurements at baseline, post-intervention, after 3, 6, and 9 months, 1 year following PPI completion, and 1 year following treatment completion. A key outcome is positive mental health, consisting of emotional, social, and psychological wellbeing. Other outcomes include, for instance, resilience, psychological complaints, quality of life, societal costs, and adherence.

**Discussion:**

Introducing a transdiagnostic eHealth PPI to various patients awaiting mental health treatment and their loved ones may improve treatment outcomes. Enhancing resilience through an eHealth PPI may reduce healthcare costs and health-related societal costs, potentially making it a cost-effective strategy compared to TAU.

**Trial registration:**

NL-OMON57370. Registered in the Overview of Medical Research in the Netherlands on 17 March 2025.

**Supplementary Information:**

The online version contains supplementary material available at 10.1186/s40359-025-03860-0.

## Background

Mental healthcare systems are facing increased care demands amidst staff shortages, resulting in prolonged waiting times for mental health treatment [1]. To address this challenge, certain countries have established national benchmarks to improve waiting times in mental healthcare, including Denmark, Finland, Ireland, Lithuania, New Zealand, Norway, Spain, United Kingdom, and The Netherlands [2]. Notably, up to 75% of patients with common mental health conditions are currently being treated within 6 weeks in the United Kingdom [2]. In The Netherlands, insurers and healthcare providers have agreed on a maximum acceptable waiting period of 14 weeks for most conditions (i.e., the Dutch Treeknorm) [3]. However, this norm is often not met in Dutch mental healthcare, as waiting times for patients exceed 14 weeks in approximately 30% of all cases [4]. This is problematic, as time spent on a waiting list is negatively associated with desirable treatment outcomes, including improvement and recovery [5]. In addition, it is associated with increased drop-out rates during treatment [6, 7] and increased costs for interim care provided by General Practice Mental Health Professionals (GP-MHP), which is used to bridge the waiting time [8]. While waiting, prospective patients may experience aggravating symptoms [9], compromising adequate recovery [10, 11]. In addition, aggravation of mental health symptoms is associated with decreased quality of life, delays in educational achievement [12], reduced productivity and increased absenteeism in the workspace [13, 14], causing a substantial burden of illness [15].

Apart from the costs within the healthcare sector, the societal costs of mental illness mostly manifest outside the healthcare sector [16]. Importantly, the annual excess cost per capita of having any common mental disorder is approximately €3,200 in The Netherlands [16]. Even though GP-MHP care may be delivered to some patients awaiting treatment, a structured treatment plan to bridge the waiting time is often not guaranteed [3], potentially causing patients to utilize other healthcare resources [15]. Although cost estimates of waiting times prior to receiving mental health treatment are not fully known on the population level, the waiting time itself is considered a predictor of mean economic costs for depression and anxiety disorders across all levels of clinical severity [17].

As waiting lists cannot be easily reduced in the short term, a potential alternative is to examine whether offering an online, resource-based intervention during the waiting period could improve existing treatment protocols for various patients awaiting mental health treatment. Resource-based interventions, including Positive Psychology Interventions (PPIs), aim to strengthen mental resources in human beings, including resilience [18]. In short, PPIs are empirically supported and aim to cultivate resilience by increasing positive factors (e.g., optimism, self-compassion) [19, 20]. In general, PPIs may help individuals cope with challenging situations and, in turn, increase wellbeing [18]. Enhancing protective factors may also reduce risk factors contributing to psychopathology [21]. Since GP-MHP care is not structurally available for all patients due to high demand during the waiting period, offering an evidence-based eHealth PPI may be an adequate alternative to reduce staff costs and to improve timely access to hybrid mental healthcare, potentially making it an effective and low-cost intervention.

The clinical effectiveness of PPIs has been demonstrated in patients with depression, anxiety and chronic pain [21–23]. Although it is currently unknown whether a transdiagnostic eHealth PPI could be effective in other mental disorders (e.g., autism spectrum disorder and personality disorders) due to a lack of prior studies, it is worth exploring whether a transdiagnostic eHealth PPI can be applied more broadly. There are no theoretical underpinnings for suboptimal PPI outcomes in other study populations. In contrast, PPIs were even able to produce meaningful clinical outcomes in a high-risk cohort of inpatients with suicidal complaints [24], highlighting their potential usefulness.

In most cases, the patient’s loved ones (e.g., partner, family, friends, colleagues) are not involved in treatment, even though it is well established that interpersonal connections, such as connections with loved ones, may further promote patient recovery [25]. Furthermore, research suggests that positive activities could promote positive relationships with others, which may mitigate interpersonal risk factors like loneliness [19]. Importantly, loved ones often become caregivers for patients, which may cause them to feel burdened. Consequently, loved ones may experience mental health complaints as well, requiring more demand for psychological care [26]. The effects of psychological interventions may be enhanced by involving the patient’s social network, as this may yield synergistic effects that strengthen an intervention’s overall impact [27]. Hence, PPIs targeting both patients and their loved ones may enhance patient recovery and yield positive effects among loved ones who may also experience mental health complaints.

While the clinical effectiveness of PPIs has been demonstrated systematically [21, 28–31], evidence on their cost-effectiveness — apart from two encouraging studies conducted in the general Dutch adult population by Schotanus-Dijkstra, Drossaert [32] and Bolier, Majo [33] — remains limited. In addition, the clinical effectiveness and cost-effectiveness of combining an eHealth PPI with a subsequent mental health treatment have generally not been evaluated, nor have these objectives been examined within a heterogeneous research population containing patients with various mental health conditions and their loved ones. To address these research gaps, an eHealth positive psychology intervention (eHealth PPI) will be developed, characterized by transdiagnostic treatment principles that can be applied broadly across mental health conditions. The proposed eHealth PPI will target transdiagnostic factors to support patients with various mental health conditions awaiting outpatient treatment and their loved ones. Addressing these gaps is highly relevant, especially in light of contemporary attempts to enhance the clinical value and financial sustainability of Dutch mental healthcare [34], such as the increasing focus on providing hybrid care [35]. Within hybrid mental healthcare, various eHealth applications are likely cost-effective, since they are generally considered cost saving for a range of mental disorders [36, 37]. In addition to assessing (cost-)effectiveness, evaluating procedural implementation is key for clinical practice. In order to avoid long term implementation barriers, digital mental health interventions should be financially and legally implementable within the organizational constraints of healthcare systems [38]. To optimize intervention success among participants, gathering data on its feasibility, acceptability, accessibility, adherence and engagement is imperative [39].

Considering the aforementioned research gaps, we aim to expand the scope of knowledge on eHealth PPIs and their transdiagnostic applications, and clinical and financial implications. To facilitate reproducibility and transparency of all scheduled methods in advance [40], a comprehensive study protocol was developed. In light of this purpose, the current paper presents a study protocol aimed at examining the (cost-)effectiveness and feasibility of an eHealth PPI for patients with various psychological complaints awaiting mental health treatment and for their loved ones.

## Objectives

Two experimental conditions will be established involving the eHealth PPI during the waiting period for [1] patients only and [2] for patients and their loved ones. Primarily, both experimental conditions will be compared to a [3] treatment as usual (TAU) condition, involving patients who will not receive the eHealth PPI during their waiting period. However, conditions 1 and 2 will also be compared to each other exploratively. In all three conditions, patients will receive a mental health treatment as usual after the waiting period. Using these three RCT conditions and a small pilot study (replicated single-case design), the study protocol will address objectives and hypotheses from three areas of expertise:

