#### A priori sample size

The a priori sample size in study 2 is based on the anticipated change in positive mental health between baseline and one-year treatment follow-up at the clinical setting in the intervention conditions compared to the control group. Compared to arm 3 (i.e., TAU), a medium effect size of Hedges’ g = 0.45 is assumed for both PPI arms followed by a mental health treatment (i.e., arms 1 and 2). The effect size of Hedges’ g = 0.45 is conservatively estimated based on prior studies about PPI effectiveness [21, 45], assuming an overlap in treatment mechanisms when combining a PPI with a subsequent mental health treatment. The Mental Health Continuum – Short Form (MHC-SF) is defined as the primary outcome [46], which is justified in the section on ‘’Data collection’’. Using a pretest-posttest design for this primary outcome, the required sample size was estimated at 207 patients, including 69 patients per treatment arm under a 5% Type I error rate, 80% statistical power, and an equal allocation ratio. While the PPI + mental health treatment arm including loved ones (arm 2) is expected to yield a larger effect size than the PPI + mental health treatment arm without loved ones (arm 1), the actual difference between both effect sizes is unknown due to the novelty of the inclusion of loved ones. In the absence of previous studies, we will conservatively assume identical effect sizes for both arm 1 and arm 2, which can be compared to arm 3 (TAU) with a sufficient degree of certainty. In addition, we still aim to compare arm 1 to arm 2 exploratively, knowing that these specific comparisons may not be adequately powered. Assuming a 35,5% attrition rate between baseline and the 1-year follow up measurement following treatment completion based on previous findings [47, 48], a total sample size of 207/(1–0.355) = 321 participants (*n* = 321) is required, yielding 107 patients per treatment arm. Since the second arm involves one loved one per patient, this arm will contain 214 participants. Thus, a total sample size of 428 participants will be required, including 321 patients and 107 loved ones.

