## Data analysis

All analyses of (cost-)effectiveness will be performed in accordance with the Intention-To-Treat (ITT) principles, meaning that data from all participants will be analysed according to the study condition to which they were initially assigned, regardless of adherence [94]. Assessment of baseline inequalities between study conditions will be performed and followed up, if needed. Due to the longitudinal nature of study 1 and study 2, dropout and other processes causing missing data are expected [95]. Appropriate missing data handling techniques will be applied after assessment of the magnitude, mechanisms, and patterns of missing data [96]. A one-sided alfa of 0.05 will be applied in both studies. Since multiple comparisons between RCT arms will be performed in study 2, this significance level of 0.05 will be adjusted to manage Type I error probability, using the Holm-Bonferroni method [97].

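### Holm-Bonferroni is valid but slightly conservative for two primary contrasts that share one TAU arm; naming that two-contrast family and using step-down Dunnett would recover a little power

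*Protocol article*

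**What the plan says.** The Objectives section sets the primary comparisons: "Primarily, both experimental conditions will be compared to a [3] treatment as usual (TAU) condition". It adds that "conditions 1 and 2 will also be compared to each other exploratively". The RCT design section fixes 1:1:1 allocation.

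The opening of Data analysis sets the test level: "A one-sided alfa of 0.05 will be applied in both studies". It then gives the reason for adjusting, "Since multiple comparisons between RCT arms will be performed in study 2", and the method: "this significance level of 0.05 will be adjusted to manage Type I error probability, using the Holm-Bonferroni method". It does not list the comparisons in the family. The primary clinical analysis is an ANCOVA of the MHC-SF at 12 months post-PPI across the three arms, with the pre-PPI score as covariate.

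The A priori sample size section sets Hedges' g: "0.45 is assumed for both PPI arms followed by a mental health treatment". It also states that "we will conservatively assume identical effect sizes for both arm 1 and arm 2". It arrives at 207 completers, "including 69 patients per treatment arm under a 5% Type I error rate, 80% statistical power, and an equal allocation ratio".

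**The concern.** Two treatments compared with one control is the setting for which Dunnett-type procedures were built. Chance variation in the TAU mean moves both contrasts the same way, so their correlation is known from the design. Holm-Bonferroni must hold under any correlation, so its first threshold is a little stricter than this design needs. The unused part of the 5% is power given up.

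The undefined family is the second strand. The adjustment is justified by comparisons between RCT arms in general, and the trial will make three pairwise comparisons. If the exploratory arm 2 versus arm 1 contrast entered the Holm family, the two primary contrasts would pay for a test that the protocol elsewhere treats as exploratory and possibly underpowered.

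**Working it through.** **Inputs.** From the protocol article: two primary contrasts with shared TAU; 1:1:1 allocation; one-sided 0.05 with Holm; g = 0.45 for both PPI arms; 69 completers per arm; 35.5% attrition. Not given: the correlation between baseline and 12-month MHC-SF. I take 0 (no covariate gain) and an assumed range of 0.3 to 0.6.

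**The plan's own figure.**
- One unadjusted one-sided 5% contrast needs 2(1.645 + 0.842)²/0.45² = 61.1 per arm, or 62 with t tests.
- At one-sided 2.5% it needs 2(1.960 + 0.842)²/0.45² = 77.5, so 78. Neither gives 69.
- Holm over two one-sided contrasts with both effects 0.45, simulated with pairwise t tests, gives 79.7% power per contrast at 68 per arm and 80.3% at 69. So 69 is the smallest number reaching 80%.
- Then 69 × 3 = 207 and 207/(1 − 0.355) = 320.9, so 321.

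The protocol does not state this route, and it is not the only one. One-sided 2.5% with an ANCOVA baseline correlation of 0.33 gives 77.5 × (1 − 0.33²) = 69.1.

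**Correlation.** With equal arms and equal variances, Cov(A1 − TAU, A2 − TAU) = σ²/n and each contrast has variance 2σ²/n, so the correlation is 0.5.

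**Thresholds.** Let Z1 and Z2 be the two statistics.
- Holm: first step z > 1.960 (p < 0.025), second step z > 1.645.
- Step-down Dunnett: the first step c solves P(Z1 ≤ c, Z2 ≤ c) = 0.95 at correlation 0.5, so c = 1.916 (nominal p 0.0277). The second step is also 1.645.
- Holm's family-wise error when neither arm works is 1 − P(Z1 ≤ 1.960, Z2 ≤ 1.960) = 4.54%. Dunnett's is 5.0% by construction.
- The second steps are equal and Dunnett's first threshold is lower, so Dunnett rejects whenever Holm does.

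**Power at 69 per arm** (normal approximation). The noncentrality is 0.45 × √(69/2) = 2.643, divided by √(1 − ρ²) for baseline correlation ρ. Contrast 1 is rejected if Z1 > c, or if Z1 > 1.645 and Z2 > c.

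| ρ | Both arms work: per contrast, Holm → Dunnett | Only one arm works: its contrast, Holm → Dunnett |
|---|---|---|
| 0 | 80.8% → 81.4% (+0.6) | 75.3% → 76.7% (+1.3) |
| 0.3 | 84.2% → 84.8% (+0.5) | 79.2% → 80.4% (+1.2) |
| 0.5 | 90.4% → 90.7% (+0.3) | 86.3% → 87.2% (+0.9) |
| 0.6 | 94.1% → 94.3% (+0.2) | 91.1% → 91.7% (+0.7) |

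Gains are taken before rounding. With ρ = 0 and both arms effective, the chance of at least one positive contrast rises from 88.2% to 89.1%. With t tests, 80% per contrast needs 68 per arm under Dunnett and 69 under Holm, a saving of one completer per arm.

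**If the family held all three pairwise comparisons.** Holm with first step p < 0.05/3, simulated with t tests at 69 per arm, ρ = 0, both effects 0.45 and the third contrast taken as arm 2 better than arm 1, gives 72.7% per TAU contrast. Two-contrast Holm gives 80.3% and step-down Dunnett 81.1%. Of the 8.4 points between 72.7% and 81.1%, 7.6 come from naming the family and only about 0.8 from the rest of the change.

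**The case against.** The strongest reply is that nothing is wrong. Holm is valid and needs no joint-distribution assumption. The stated 69 per arm is also consistent with a calculation in which Holm is already paid for. All of that stands. A reader might infer from the 4.5% figure that Holm breaks the error rate, or that it leaves the trial short of its 80%. The documents support neither: Holm errs on the safe side, and with two contrasts it reaches 80% at 69 per arm on the plan's assumptions.

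It is also fair that the zero-covariate case overstates the gain, because the planned analysis is an ANCOVA. The table therefore shows the range.

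A third point concerns the unblinded sample-size re-estimation, which uses the smaller observed effect. Since the final size depends on the data, the fixed-design 5.0% for Dunnett cannot be promised, and Holm's slack might look useful. In simulations with assumed re-estimation rules, Holm stayed at about 4.6 to 4.7% when neither arm worked, against about 5.1 to 5.2% for Dunnett. When one arm worked, both exceeded 5% alike, at about 5.2 to 5.8%. Those rules are assumptions, and the cited Bayesian method may control the error itself. The issue does not favour Holm, but it does qualify the 5% for either procedure.

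Lastly, a reader might infer that the plan does put arm 2 versus arm 1 in the Holm family. The text does not say so, and the Objectives section calls that comparison exploratory. The 73% is what one reading would cost, not what the plan commits to. Likewise, the primary objective names both 6 and 12 months, while the primary analysis names 12 months only. The two-contrast figures rest on the latter.

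**Conclusion.** The point holds as a low-severity efficiency improvement. For two one-sided contrasts sharing a TAU arm, Holm uses 4.5% of the allowed 5% in a fixed design when neither arm works, and step-down Dunnett is never less powerful. At the planned size and effect this is worth between 0.2 and 0.6 points per contrast, or 0.7 to 1.3 points if only one PPI version works. Under the plan's assumptions that is about one completer per arm.

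The more useful part of the change is an explicit family. It rules out the three-comparison reading, which would lower power per TAU contrast to about 73% at 69 per arm with no covariate gain.

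The figures assume equal completers and equal variances (correlation 0.5), approximate joint normality, a family of two contrasts at 12 months, and an assumed baseline correlation where one is used.

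**What to change.** In the opening part of Data analysis:

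- Define the primary confirmatory family as arm 1 versus TAU and arm 2 versus TAU on the MHC-SF at 12 months post-PPI.
- Keep arm 2 versus arm 1 outside that family as exploratory.
- Test the two contrasts by step-down Dunnett, one-sided at family-wise 0.05, with critical values taken from the ANCOVA contrast covariance matrix. That also handles unequal dropout, when the correlation is no longer exactly 0.5.

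If the team prefers to keep Holm, the first two items alone secure most of the benefit.

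The cost is a sentence or two and a standard software option, with no extra patients, visits or data. The added reliance is on joint normality of the two contrasts, which is reasonable at about 69 per arm. Whichever procedure is chosen must be carried through the sample-size re-estimation and its effect on the 5% level checked there. The change should be made before any unblinded interim data exist.

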### Clinical effectiveness

#### Primary objective

Our primary clinical aim is to examine whether offering the eHealth PPI to various patients during the waiting period and their loved ones, followed by a mental health treatment for patients, is clinically effective in terms of improving positive mental health scores (primary outcome) at the 6-month and 12-month post-PPI measurement, compared to TAU. We hypothesize that introducing this eHealth PPI in condition 1 (PPI for patients only) and in condition 2 (PPI for patients and loved ones), followed by a mental health treatment, is clinically more effective, compared to condition 3 (TAU).

#### Secondary objective

Our secondary clinical aim is to evaluate whether offering the proposed eHealth PPI simultaneously to both patients and their loved ones during the waiting period (condition 2), followed by a mental health treatment for patients, is clinically superior to only involving patients in the eHealth PPI (condition 1). In addition, individual trajectories will be modelled to explore which patients are most likely to benefit from the eHealth PPI.

